## Abstract

**Background:**

Uganda accounts for 5% of all malaria cases and deaths reported globally and, in endemic countries, pregnancy is a risk factor for both acquisition of *P. falciparum* infection and development of severe malaria. In recent years, malaria control has been threatened by COVID-19 pandemic and by the emergence, in Northern Uganda, of both resistance to artemisinin derivatives and to sulfadoxine-pyrimethamine.

**Methods:**

In this facility-based, prospective, observational study, pregnant women will be recruited at antenatal-care visits and followed-up until delivery. Collected data will explore the incidence of asymptomatic parasitemia and malaria-related outcomes, as well as the attitudes towards malaria prevention, administration of intermittent preventive treatment, healthcare seeking behavior and use of insecticide-treated nets. A subpopulation of women diagnosed with malaria will be recruited and their blood samples will be analyzed for detection of genetic markers of resistance to artemisinin derivatives and sulfadoxine-pyrimethamine. Also, to investigate the impact of COVID-19 on malaria care among pregnant women, a retrospective, interrupted-time series will be conducted on at the study sites for the period January 2018 to December 2021.

**Discussion:**

The present study will explore the impact of COVID-19 pandemic on incidence of malaria and malaria-related adverse outcomes, along with the prevalence of resistance to artemisinin derivatives and to sulfadoxine-pyrimethamine. To our knowledge, this is the first study aiming to explore the combined effect of these factors on a cohort of pregnant women.

*Trial registration*: This study has been registered on the ClinicalTrials.gov public website on 26th April, 2022. ClinicalTrials.gov Identifier: NCT05348746.

## Background

### Malaria epidemiology and COVID-19

Over the last twenty years, tremendous progress has been made on malaria control, averting an estimate of 1.5 billion cases and saving 7.6 million lives. However, despite the astonishing results achieved in the last two decades, COVID-19 pandemic added a crucial challenge to the fight against the disease. On one side, malaria control relies heavily on individual choice to seek care, and early messaging targeted on reducing SARS-CoV2 transmission advised people to stay home in case of fever. On the other side, supply chains that allow the delivery of malaria commodities, such as insecticide-treated nets or antimalarial drugs, have been disrupted, and healthcare workforce constrained. All these factors contributed to a reverse of the reducing trend in malaria cases and deaths that shifted, respectively, from 227 million and 534,000 in 2019 to 241 million and 602,000 in 2020 [1].

According to the latest WHO World Malaria Report [1], Uganda accounts for 5% of all malaria cases reported globally. Oyam and Kole districts, selected for the study, are among the most affected areas in the country with, respectively, 407 and 361 new cases per 1000 inhabitants in 2019 [2]. In this context, particularly affected are children under five years of age (U5) and pregnant women. In the area where the project will operate, the rate of pregnant women that receives 3 or more doses of intermittent preventive treatment (IPTp) is less than 48% [2].

Concerning the impact of COVID-19 on malaria care in Uganda, a study conducted by Namuganga et al. [3]—except for a modest decrease in the proportion of malaria cases treated with ACT—documented no major effects on malaria disease burden. However, the study did not evaluate the impact of COVID-19 on antenatal care and malaria-related maternal outcomes. At this regard, in the pre-pandemic period (years 2018–2019) the mean antenatal care (ANC) attendance in the district of Oyam was of 1721 first visits per month, while an average of 472 women per month received at least 3 doses of IPTp.

### Pregnancy associated malaria

#### Intermittent preventive treatment

In hyperendemic areas, pregnancy is a risk factor for both acquisition [4] of *P. falciparum* infection and for development of severe malaria [5]. Younger women, primi- or secundigravidae and HIV + women are particularly at risk [6]. Adverse outcomes for mothers and their infants include maternal anemia, low birthweight, prematurity, placental malaria, infant malaria, infant anemia and congenital malaria. Furthermore, adverse events are exacerbated by poor maternal nutritional status [7] and HIV coinfection [8].

Apart from consistent use of ITN, malaria control in this population is based on two pillars: intermittent preventive treatment of asymptomatic women and appropriate management in case of illness [9]. IPTp with sulfadoxine-pyrimethamine (SP) is still highly cost-effective in preventing the adverse consequences of malaria on maternal and foetal outcomes, even in areas with a high prevalence of quintuple mutant parasites [10], but coverage remains unacceptably low in several African countries [11]. For HIV-negative pregnant women, IPTp consists in the administration of at least three doses of SP (1500 mg sulfadoxine/75 mg pyrimethamine), in three antenatal care visits, starting early in the second trimester and at least four weeks apart [9].

In HIV negative women, a promising alternative to SP for IPTp is dihydroartemisinin-piperaquine (DHA-PPQ, 3 full strength tabs, 40 mg/320 mg, given once a day for 3 consecutive days), that showed to be more efficacious in reducing maternal malaria parasitemia and anemia at delivery, stillbirths and early infant mortality. In fact, SP efficacy may be decreased in areas with very high drug resistance and consistent presence of sextuple mutant haplotypes of *P. falciparum* [12]. However, there is no consensus as to the level of resistance at which SP-IPTp should be discontinued and an alternative regimen substituted.

For HIV positive patients, the current WHO guidelines recommend daily co-trimossazole prophylaxis.

#### Diagnosis and treatment

In most endemic countries, diagnosis heavily relies on the use of rapid diagnostic tests (RDT) which, however, are insufficiently sensitive in detecting the so-called subpatent infections—asymptomatic infections with low parasite densities—and infections due to parasites carrying the pfhrp2 and pfhrp3 gene deletions [13]. These limitations are partly overcome by microscopy and PCR-based tests, that can detect also low parasitemia [14], but the clinical impact of such infections is still matter of debate [15].

Treatment of malaria differs according to gestational age. For women in their first trimester with uncomplicated *P. falciparum* malaria, WHO recommends 7 days of quinine + clindamycin. From the second trimester on, experience with artemisinin derivatives is increasingly reassuring: no adverse effects on the mother or foetus have been reported. Thus, treatment of uncomplicated *P. falciparum* malaria consists of three-day course of oral artemisinin-based combination therapy (ACT). On the other side, treatment of severe malaria does not differ from the one prescribed to non-pregnant women. Parenteral artesunate is the treatment of choice in all trimesters.

### Resistance to sulfadoxine-pyrimethamine and artemisinin derivatives

Another substantial challenge for malaria case-management is resistance to first line drugs, namely artesunate and ACT. A recent paper published by Balikagala et al. documented, for the first time in African history, the presence of artemisinin resistance in a longitudinal study conducted in Gulu, Uganda [16]. According to this study, single-nucleotide polymorphisms haplotypes associated with artemisinin resistance (i.e., mutations involving the gene locus *kelch13*) clearly showed the substantial difference of haplotypes between A675V isolates in Uganda and in Southeast Asia, which suggested that the mutation probably emerged independently in Africa and Southeast Asia. In Africa, potential factors that may contribute to a delayed emergence and spread of artemisinin resistance are the extent of acquired immunity, the rate of polyclonal infections and of chronic asymptomatic infections [17]. However, the constant selective pressure exerted by the widespread use of ACT pose a substantial threat for the emergence of clinically relevant forms of resistance.

Furthermore, a study conducted by Mbonye et al. [18] in 2015 documented a baseline prevalence of *Pfdhfr* and *Pfdhps* mutations—conferring resistance to SP in *P. falciparum*—to be 89% for the quintuple mutated haplotype and 3.9% for the sextuple mutated haplotype, reaching 16.7% after one dose of SP. Today’s prevalence of the sextuple mutated haplotypes, potentially impairing the effectiveness of SP-IPTp is not known. Conceptual framework of the study is provided in Fig. 1.

**Fig. 1 Fig1:**
[figure not shown]
Conceptual framework showing the possible impact of COVID-19 and antimalarial resistance on malaria care among pregnant women. Dashed line (green): antimalarial resistance; Dotted line (blue): COVID-19; Continuous line (yellow): both COVID-19 and antimalarial resistance

## Methods

### Study design

This will be a facility-based, prospective observational study, using quantitative methods of data collection. Semi-structured questionnaires will be administered to collect the data. The study will be conducted on three separate populations, that is: “Cohort of pregnant women”, “Antimalarial resistance sub-population”, and “COVID-19 impact population” for which study methods are described separately.

#### Cohort of pregnant women

The data will be collected following a cohort of pregnant women presenting to antenatal care visits. We shall have both a retrospective cohort for the period January 2018 to December 2021 to determine the Impact of COVID-19 pandemic on malaria control and a prospective cohort for the period July 2022 to June 2024 to determine the incidence of malaria related adverse maternal and foetal outcomes. For the prospective cohort, recruitment will take place at ANC clinic. Collected data will explore the practices towards malaria prevention during the COVID-19 pandemic, malaria and COVID risk-perception and use of insecticide-treated nets, while and follow up will investigate access to antenatal care visits, administration of IPTp, healthcare seeking behaviour in case of fever. Follow-up will end at delivery, when maternal and foetal outcomes will be collected.

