#### COVID-19 impact population

To investigate the impact of COVID-19 pandemic on malaria care, we will conduct a retrospective time-interrupted series. Data will be collected at multiple and equally spaced time points (monthly) comparing trends in two different time periods: “pre-pandemic”, from January 2018 to December 2019, and “during pandemic”, from January 2020 to December 2021. Facility-based aggregate data will be extracted about the following indicators: total admissions in maternity ward, total deliveries in maternity unit, women presenting to first ANC contact, women presenting to fourth ANC contact, administration of at least one dose of IPTp, administration of at least three doses of IPTp, number of pregnant women presenting to outpatient visits, number of pregnant women diagnosed of malaria during outpatient clinic, number of pregnant women diagnosed of severe malaria, total number of stillbirths.

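### No planned data hold both COVID-19 period and drug resistance, so their combined effect cannot be estimated; the COVID-19 series also omits preterm birth and low birthweight

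*Protocol article*

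**What the plan says.** The abstract's Discussion sets two aims that involve COVID-19. The first: "The present study will explore the impact of COVID-19 pandemic on incidence of malaria and malaria-related adverse outcomes". The second is a claim of novelty, taking COVID-19 and resistance together: "this is the first study aiming to explore the combined effect of these factors on a cohort of pregnant women".

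The Methods divide the work by calendar period. Under Study design, Cohort of pregnant women, there is "a retrospective cohort for the period January 2018 to December 2021 to determine the Impact of COVID-19 pandemic on malaria control", and there is "a prospective cohort for the period July 2022 to June 2024" whose purpose is "to determine the incidence of malaria related adverse maternal and foetal outcomes". The same section says of the prospective women: "Collected data will explore the practices towards malaria prevention during the COVID-19 pandemic".

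The COVID-19 impact population section describes the retrospective part as monthly facility aggregates. It compares January 2018 to December 2019 with a pandemic segment running "from January 2020 to December 2021", and gives its aim as the impact on malaria care. Blood samples for resistance (Antimalarial resistance population) are collected from July 2022 to June 2024.

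**The concern.** To estimate a combined effect of two factors, at least one data set must contain both, and both must vary in it. Here COVID-19 period varies in one source and resistance is measured in another, at different times. No later choice of model can supply the missing variation, so this is not a detail to be left to an analysis plan.

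The adverse-outcome aim has a related weakness. Preterm birth, on which the prospective cohort is sized, and low birthweight are measured only after the series has ended, with no pre-pandemic or pandemic values beside them. If the abstract's aims carry over into the report, it would claim a joint effect that no planned data can show, and an effect of COVID-19 on birth outcomes for which no comparison exists.

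**Working it through.** No stated figure is at issue; the point rests on dates and on lists of variables. The cohort's sample size (705 per group, preterm birth 0.075 against 0.039) does reproduce with the continuity-corrected formula (650 without it). It compares women with and without malaria and has no COVID-19 or resistance term, so nothing here depends on it.

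**Step 1: calendar coverage.** Dates are from the three Study design subsections. Months = 12 × (end year − start year) + (end month − start month) + 1.

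- Pre-pandemic segment, January 2018 to December 2019: 12 × 1 + 11 + 1 = 24.
- Pandemic segment, January 2020 to December 2021: 12 × 1 + 11 + 1 = 24.
- Prospective cohort and resistance sampling, July 2022 to June 2024: 12 × 2 − 1 + 1 = 24.
- Covered by neither, January to June 2022: 5 + 1 = 6.
- Shared by the series and the prospective data: 0.

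**Step 2: what each source contains.**

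| | Series 2018–2021 | Prospective data 2022–2024 |
|---|---|---|
| Level | monthly facility counts | individual women |
| Pre-pandemic against pandemic contrast | yes, 24 points each side | none |
| Resistance genotypes | none | yes |
| Outpatient malaria, severe malaria | counts | individual diagnoses |
| Stillbirth | count | individual |
| Preterm birth, low birthweight | none | individual |

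In the left column resistance is absent. In the right column every woman belongs to the same period, outside both segments of the series. Neither column, nor the two together, gives outcomes by resistance status in more than one COVID-19 period, so a combined effect is not identified.

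**Step 3: adverse birth outcomes.** The delivery row of Table 1 lists stillbirth, low birthweight and preterm birth; Data analysis adds miscarriage. That makes four. Of the series' ten indicators, one (stillbirth) is among them, so coverage is 1 of 4.

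**Step 4: what the series can answer.** Its other nine indicators are maternity admissions, deliveries, first and fourth antenatal contacts, at least one and at least three IPTp doses, outpatient visits, outpatient malaria and severe malaria. These serve the stated aim on malaria care. As counts, outpatient malaria, severe malaria and stillbirth also serve part of the abstract's aim.

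**The case against.** The strongest reply is that the combined effect appears only in a novelty sentence in the abstract. The Methods treat the three populations separately, and no hypothesis, sample size or analysis depends on a joint effect, so no planned analysis fails. That stands. The fault is in what the article promises, which is why rewording cures most of it.

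Second, a reader might infer that none of the COVID-19 objectives can be met, or that stillbirth is the only relevant outcome in the series. The documents do not support either. The series fits its own aim on malaria care, and outpatient and severe malaria are also among its indicators. Severe malaria is treated as an outcome in Data analysis.

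Third, a reader might infer that the pandemic was over when the cohort began, and that its questionnaire cannot concern pandemic practice. The article gives no end date for the pandemic; December 2021 only closes a segment of the series. A questionnaire from July 2022 could ask about earlier practice by recall, and it does ask about current COVID-19 risk perception. The sentence is therefore unclear, not shown to be wrong. Risk perception may vary between women, but it is an attitude and does not replace a contrast between pandemic periods.

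Fourth, the retrospective part is called a cohort in one place and a census of mothers in Sample size estimation, which might suggest individual records. The only data described for it are aggregate counts, and resistance sampling begins in July 2022 in any case. Nor do genotypes come from the prospective cohort alone: a separate resistance population is recruited, over the same 2022–2024 dates.

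**Conclusion.** The point holds in a limited form. The combined effect of COVID-19 and resistance cannot be estimated from any planned data: the two sources share 0 months, and no source has both factors varying. The effect of COVID-19 on preterm birth and low birthweight cannot be estimated either, because both are collected only from July 2022. The effect on malaria care, and on counts of outpatient malaria, severe malaria and stillbirth, can be addressed with 24 monthly points on each side.

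This rests on the dates and indicator list as printed, and on reading COVID-19 exposure as the period contrast the plan itself defines. It needs no assumption about when the pandemic ended.

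**What to change.** 1. In the abstract's Discussion, replace the combined-effect claim with separate descriptions of the two factors, and limit the COVID-19 claim to outcomes in the monthly series. This costs wording only and is enough by itself to align the aims with the data.
2. Add monthly counts of low-birthweight and preterm births for 2018–2021 to the COVID-19 impact extraction, with total deliveries (already an indicator) as denominator, where the maternity records hold them. Their availability and completeness are assumptions, since the article does not describe these records. The cost is some extra extraction work; no participants or procedures are added.
3. Under Cohort of pregnant women, state whether the pandemic-practice questions concern recalled 2020–2021 practice or current 2022–2024 practice, and report the answers under that label.

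Extending the series to June 2024 would add 30 monthly points (48 to 78) and cover the cohort's months. This is optional: it creates no resistance data before July 2022, so it would not make the combined effect estimable.

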#### Antimalarial resistance population

To estimate the epidemiological burden of resistance to first-line drugs for treatment and prevention of malaria in pregnant women, a separate sub-population of women diagnosed with positive malaria parasitaemia will be recruited. Prevalence of antimalaria resistance will be evaluated with a cross-sectional analysis of genetic polymorphisms in plasmodium parasites isolated from blood samples collected for the period July 2022 to June 2024. Individuals eligible for this subpopulation will be all pregnant women presenting with microscopically confirmed *P. falciparum* malaria in the study sites. For individuals included in this population, clinical data will be collected, and blood samples to be sent to Italian National Institute of Health, Rome, for detection of genetic markers of resistance to artemisinin derivatives and sulfadoxine-pyrimethamine.

#### COVID-19 impact population

To investigate the impact of COVID-19 pandemic on malaria care, we will conduct a retrospective time-interrupted series. Data will be collected at multiple and equally spaced time points (monthly) comparing trends in two different time periods: “pre-pandemic”, from January 2018 to December 2019, and “during pandemic”, from January 2020 to December 2021. Facility-based aggregate data will be extracted about the following indicators: total admissions in maternity ward, total deliveries in maternity unit, women presenting to first ANC contact, women presenting to fourth ANC contact, administration of at least one dose of IPTp, administration of at least three doses of IPTp, number of pregnant women presenting to outpatient visits, number of pregnant women diagnosed of malaria during outpatient clinic, number of pregnant women diagnosed of severe malaria, total number of stillbirths.

### Eligibility criteria

#### Cohort of pregnant women

Inclusion criteria:

All pregnant women at any gestational age presenting to the study sites, both at the emergency department, outpatient or ANC clinic will be eligible to participate in this study. Inclusion criteria will be:

Pregnancy confirmed by obstetrical visit, positive urine pregnancy test or intrauterine pregnancy by ultrasoundProvision of informed consentPlan to deliver in the hospital

Exclusion criteria:Ongoing labor or delivery

#### Antimalarial resistance population

All pregnant women presenting to Aber Hospital and selected healthcare facilities with microbiologically confirmed malaria will be eligible for recruitment.

Inclusion criteria:Microscopically-confirmed diagnosis of malariaPregnancy confirmed by obstetrical visit, positive urine pregnancy test or intrauterine pregnancy by ultrasoundProvision of informed consentAgreement to avoid antimalarial medications given outside the Uganda Clinical Guidelines [19]

Exclusion criteria:Too ill to participate in the study according to clinician judgmentIntake of any antimalarial medication before recruitment

### Sample size estimation

#### Sample size estimation

COVID-19 impact population

For the retrospective cohort investigating the impact of COVID-19, we shall use a *facility-based census* to include all pregnant mothers who sought care at the study sites for the period January 2018 to December 2021.Prospective çohort of pregnant women

For the prospective cohort, the sample size was estimated using the sample size estimation function in STATA12 for two-sample comparison of proportions. Null hypothesis: p1 = p2, (no difference in preterm birth rates), where p1 is the preterm birth rate among pregnant mothers diagnosed with malaria (exposed group) and p2 is the preterm birth rate among pregnant mothers with no diagnosis of malaria (non-exposed group). Assuming a type I error, alpha, of 0.050 for two-sided hypothesis, power of the study at 0.80, p1 = 0.075 and p2 = 0.039 based on the preterm birth rates reported in the Uganda Birth Cohort Study conducted from 2014–2016 in 12 districts in rural northern and southwestern Uganda [20]. Assuming equal number of participants in both groups, the required sample sizes in each of the two groups is 705. And after factoring in 10% for non-response in both groups, the total minimum required sample size is 1552 pregnant women (776 in each of the 2 groups).Antimalarial resistance population

Given the total population of 779,600 in Oyam and Kole districts. Given that, based on Uganda bureau of statistics (UBOS), the total number of pregnant women in the two districts is expected to be 5% of the total population (n = 38,980); the expected rate of parasitemia among pregnant mother is expected to be 27% (n = 10,525) [21]; the expected resistance to sulfadoxine-pirimethamine and artemisinin-derivatives are, respectively, 16% and 20% [16, 18]; using the sample size calculation formula developed by Daniel and colleagues [22] and a margin of error, alpha = 5% the minimum required number of pregnant women diagnosed with malaria is 203. Applying 10% correction factor and assuming an increasing trend the required minimum sample size for this population is 224 cases of microscopically confirmed malaria among pregnant women.

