### Sampling procedure and selection of participants

Sampling of health Units: The study will use purposive sampling to include Aber Hospital, Aboke HCIV and Atipe HCIII as the site for enrollment. This is based on the following criteria:Already existent good laboratory capacity for diagnosis of malaria.Presence of an experienced microscopist.Antenatal care visit volumes of at least 50 visits per month.Good quality of routine service offered to patients with malaria as per periodic quality of care assessment.

Participants coming to the sampled in healthcare facilities that will meet the eligibility criteria will be included in the study. Consecutive enrollment of participants will be undertaken up to when the minimum sample size required for the study will be met.

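### The stated 80% power rests on equal groups with and without a malaria diagnosis, but consecutive enrolment does not secure that split and the plan never states the expected share diagnosed

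*Protocol article*

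**What the plan says.** In the Protocol article, under Sample size estimation, the prospective cohort is sized by a two-sample comparison of proportions. The outcome is preterm birth and the exposure is a malaria diagnosis. The inputs are "Assuming a type I error, alpha, of 0.050 for two-sided hypothesis", "power of the study at 0.80", and "p1 = 0.075 and p2 = 0.039 based on the preterm birth rates reported in the Uganda Birth Cohort Study". On the split between groups: "Assuming equal number of participants in both groups, the required sample sizes in each of the two groups is 705". On the total: "And after factoring in 10% for non-response in both groups, the total minimum required sample size is 1552 pregnant women", which the text breaks down as 776 in each group.

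The section Sampling procedure and selection of participants gives the recruitment rule: "Consecutive enrollment of participants will be undertaken up to when the minimum sample size required for the study will be met". Under Eligibility criteria, the cohort takes pregnant women at any gestational age without regard to malaria status.

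The only frequency of malaria in pregnancy in the document comes in the calculation for the antimalarial resistance population: "the expected rate of parasitemia among pregnant mother is expected to be 27" per cent.

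**The concern.** Equal groups are a design feature when the investigator controls group membership. Here the exposure is observed. Table 1 has microscopy at recruitment, at each antenatal visit (at most eight times) and at febrile visits. The ratio of exposed to non-exposed women is therefore whatever malaria frequency and test frequency produce. No quota, matching or stratification on malaria status is described, and no figure is offered for the share of women who will have been diagnosed by delivery.

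This is the only hypothesis for which the cohort is sized. If the split is far from even, the 80% does not hold, and a null result on preterm birth would be read as stronger evidence than it is. The condensed form of the article does not explain the gap: the assumption and the enrolment rule are both stated, and the rule does not deliver the assumption.

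**Working it through.** **Inputs.** From Sample size estimation: two-sided alpha 0.05 (z = 1.960), power 0.80 (z = 0.842), p1 = 0.075, p2 = 0.039, difference d = 0.036, equal groups, 10% non-response, 1552 enrolled. The exposed share is not stated, so it is varied.

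**Step 1: reproduce 705.** The mean proportion is 0.057. The uncorrected size per group is

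n = [1.960·√(2·0.057·0.943) + 0.842·√(0.075·0.925 + 0.039·0.961)]² / 0.036² = (0.6426 + 0.2751)² / 0.001296 = 649.9, or 650.

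With the continuity correction, n/4·[1 + √(1 + 4/(n·d))]² = 704.3, or 705. This matches, so the plan's figure is continuity-corrected.

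**Step 2: reproduce 1552 and check the allowance.** 705 × 1.10 = 775.5, or 776 per group and 1552 in total. This also matches. Removing 10% again gives 776 × 0.90 = 698 per group, below 705; power at 698 per group is 79.6%. Dividing instead gives 705/0.90 = 783.3, or 784 per group and 1568 in total.

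**Step 3: power when the split is not even.** Let n1 be the exposed, n2 the non-exposed and k = n2/n1. Inverting the same corrected formula:

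- effective n1: n′ = n1·[1 − (k+1)/(2·k·n1·d)]²
- pooled proportion: p̄ = (p1 + k·p2)/(1 + k)
- power = Φ{[d·√n′ − 1.960·√(p̄(1−p̄)(1+1/k))] / √(p1(1−p1) + p2(1−p2)/k)}

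Evaluable women: 1552 × 0.90 = 1397. Worked case at 27% exposed: n1 = 377, n2 = 1020, k = 2.706, n′ = 339.9, p̄ = 0.0487. Then (0.6637 − 0.4938)/0.2885 = 0.589, and Φ(0.589) = 72.2%.

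| Exposed share | Power, continuity-corrected | Power, uncorrected |
|---|---|---|
| 20% | 64.5% | 69.3% |
| 27% | 72.2% | 76.2% |
| 35% | 77.2% | 80.6% |
| 40% | 78.9% | 82.1% |
| 45% | 79.7% | 82.8% |
| 50% | 79.6% | 82.8% |
| 60% | 76.8% | 80.4% |
| 70% | 68.9% | 73.5% |

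If all 1552 women were evaluable, 27% exposed (419 versus 1133) would give 76.6% corrected and 80.0% uncorrected.

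**Step 4: what 80% power would take at 27% exposed.** The corrected formula needs about 456 exposed women, hence 456/0.27 = about 1689 evaluable and 1689/0.90 = about 1877 enrolled.

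**Step 5: the other reading of the minimum.** If 776 in each group is binding, consecutive enrolment at 27% exposed must continue to about 776/0.27 = 2,870 women. A total of 1552 fills both groups only at an exact 50:50 split.

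**The case against.** The strongest reply is that 27% is not the plan's exposure rate. It is a parasitaemia rate, brought in to estimate the number of infected women in two districts for the resistance sample. The exposed group is women ever diagnosed, and that share can build up over repeated screens and sick visits. As an illustration only: if 27% were a point prevalence and two screens were independent, 1 − 0.73² = 47% would be diagnosed, and power would be back at about 80%. A reader might infer from the 27% that equal groups are impossible, or that the true power is 72%. The documents support neither. The split is uncontrolled, not unattainable, and the 72% combines a 27% share, the full 10% loss and the continuity correction. The Data analysis section names chi-squared tests without saying whether a correction applies.

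It can also be said that 776 per group is part of the stated minimum, so enrolment might continue until both groups are full; and that the inflation shortfall is small, 1568 − 1552 = 16 women.

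All of this stands, and it limits the size of the problem. It does not supply the missing support for 1:1. Nowhere is a share near 50% stated or argued for, and power falls again above 50%. If the per-group minimum binds, the total of 1552 depends on the same unsupported split.

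**Conclusion.** The point holds in this form: the recruitment rule does not secure the split on which the 80% power depends, and the share that determines power is not stated. After the planned 10% loss, and by the plan's own formula, the effect runs from negligible (79–80% at 40–50% exposed) to material (72% at 27%, about 65% at 20%, 69% at 70%). Without the continuity correction the figure at 27% is 76%. These results take the plan's preterm birth rates as given and assume that loss is unrelated to exposure. The inflation error is real but minor: 698 rather than 705 evaluable per group, and 79.6% power even with equal groups. The comparison itself remains valid whatever the split; what is unsupported is the power claimed for it.

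**What to change.** In Sample size estimation, for the prospective cohort:

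1. Replace the equal-groups statement with the expected share of women ever diagnosed with malaria by delivery, and give its basis.
2. Restate power for 1552 enrolled and 10% lost over a range such as 20–70% exposed, saying whether a continuity correction is used. Show 27% as one scenario, not as the assumed value.
3. State whether the minimum that ends enrolment is 1552 in total or 776 in each group. If it is the latter, give the total that this implies (about 2,870 if 27% are exposed).
4. Correct the allowance for non-response to division by 0.90: 784 per group and 1568 in total under equal groups.

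If the power is simply restated, the cost is wording only and no extra participants are needed, though the stated power may become less favourable. Extra recruitment arises only if the sponsor chooses to hold 80% at a low exposed share or to keep a binding minimum per group.
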